### Language/semantic tasks

A set of computer-based language/semantic tasks is used to assess the potential effectiveness of tDCS. These tasks are carried out by patients at four time points: pre-tDCS (baseline) and 3 days, 2 weeks and 4 months after the end of the 10-day tDCS regime. The five language/semantic tasks are the following:
Semantic association task (SA)Picture naming task (NAME)Reading task (READ)Letter and category fluency task (FLU)Category judgment task (CJ)

Two additional tasks evaluating tDCS impacts on other cognitive functions are also applied:
Executive function task (EXE)Recognition of famous faces - a subtest of the French *Batterie Imagerie-Perception* (BIP).

The tasks are computer-programmed using E-Prime software (E-Prime®, Psychology Software Tools, Sharpsburg, PA, USA). Participants are comfortably seated in front of a laptop computer screen (HP EliteBook 8770w, USA) and a response box that records responses. Performance accuracy, reaction times and voice records are automatically registered by the software. The sessions are carried out in the presence of an investigator immediately after familiarization/training blocks comprising five trials for each task.

#### Semantic association task (SA)

This task assesses semantic capacities and provides the primary endpoint criterion. It is based on the principle of the Pyramid Palm Trees Test [54]. The material includes 78 French words, which are grouped into 26 trials. Each trial includes three words, two of them are semantically related (the target item and test item), while the third word is a semantically unrelated distractor. The three words are displayed on the computer screen for 8 s and the participant has to decide, using two response buttons, if the target item (on top of the screen) is associated with the test item (on the bottom of the screen, either left or right) or the distractor item (on the bottom of the screen, either left or right, opposite to the test item). Thirteen test items appear on the left and 13 on the right. The lack of response during this 8-s time interval is recorded as an error. The task assesses two category dimensions using the contrast between trials containing only living items (*n* = 13) and trials containing only non-living items (*n* = 13). Two modalities of this task are applied: a verbal modality (described above) and a picture modality that uses pictures instead of words. The language stimuli (pictures or words) used in these two tasks for “living” and “non-living” trials are matched for (1) lexical frequency, (2) number of letters, (3) familiarity of words and pictures and (4) visual complexity of the pictures. Stimuli of version 1 and version 2 of the test are also matched for these four variables. Outcome measures will focus on performance (number of correct responses), and reaction times in milliseconds. Figure 3 illustrates different trials of the task.

**Fig. 3 Fig3:**
[figure not shown]
Two trials of the semantic association (SA) test in their verbal and picture modalities. **a** Trial with living items for the verbal modality (*chenille* (caterpillar) - target item, *scarabé*e (beetle) - distractor, papillon (butterfly) - test item). **b** Trial with living items for the picture modality using the same items in a picture format. **c** Trial with non-living items for the verbal modality (*ceinture* (belt) - target item, *pantalon* (trousers) - test item, *gilet* (vest) - distractor). **d** Trial with non-living items for the picture modality using the same items in a picture format. For each trial in each modality subjects have to decide, by pressing one of two buttons in the response box, which of the items presented on the bottom of the screen is associated with the target item, on the top of the screen

#### Picture naming task (NAME)

This task evaluates lexical and semantic abilities. The material includes 40 pictures, derived from two picture-naming databases [55, 56]. Each picture is displayed on the computer screen for 8 s and participants are asked to name it aloud. Responses are voice-recorded and notified. The lack of a response during this time interval is recorded as an error. Stimuli of version 1 and version 2 of the test are matched for (1) lexical frequency of words, (2) familiarity of words and pictures and (3) visual complexity of the pictures. The task will allow for assessing (1) the number of correct responses, (2) the number of non-responses and (3) the number of semantic paraphasias. The number of correct responses and non-responses are markers of lexico-semantic abilities, and the number of semantic paraphasias is an additional marker of semantic abilities.

#### Reading task (READ)

The task provides a semantic marker in written language. During reading the phonological pathway allows for mapping each letter (grapheme) to a phoneme while the lexical-semantic pathway allows for “whole word reading” that depends on knowledge of written words [57]. The lexical-semantic route is therefore critical for reading irregular words where the grapheme-phoneme correspondence is not transparent (e.g., bear). In contrast, the phonological route is essential to read unknown or non-words. Regular words can be read through both the lexical-semantic and the phonological route. It has been shown that patients with SD have difficulties reading irregular words linked to their semantic impairment (e.g., see [58]) and performance with such irregular items will therefore provide a semantic marker. The task contains 45 stimuli: 15 irregular words, 15 regular words and 15 non-words that are matched for the number of graphemes. Each word appears on the computer screen for 8 s and subjects are asked to read them aloud. Responses are voice-recorded and registered in written form by the evaluator. The lack of response during this interval is recorded as an error. Stimuli of version 1 and version 2 of the test are also matched for the number of graphemes.

#### Verbal fluency task (FLU)

This task assesses language fluidity and access to lexical-semantic representations of words. It has two modalities: (1) in the “letter fluency” subtask participants are asked to produce, during 1 min, a maximum of words beginning with a particular letter displayed in the center of the screen; (2) in the “category fluency” subtask participants are asked to produce, during 1 min, a maximum of words belonging to a given semantic category displayed in the center of the computer screen. For the “letter fluency” subtask, stimuli of version 1 and version 2 are matched for the number of existing words starting with the given letters and also their cumulative frequencies. For the “category fluency” subtask stimuli of version 1 and version 2 are matched for the number of existing items within that category. The measured variables are the number of items produced per minute in each of the two tasks. The subjects’ responses are voice-recorded and quantified.

#### Category judgment task (CJ)

The task assesses semantic capacities in the verbal modality. The material includes 40 French words, 20 of which represent “living items” and 20 of which represent “non-living items”. Words representing “living” and “non-living” items, and words of both versions of the task, are matched for lexical frequency, number of letters and number of phonemes. Each word stimulus is displayed in the center of a computer screen for 8 s. Subjects are asked to judge whether a given word item belongs to a “living” or to a “non-living” semantic category and answer by pressing the corresponding buttons of the response box.

#### Executive function task (EXE)

This task is used as a control task to assess whether tDCS over anterior temporal regions has semantic-specific effects or whether it might impact on executive functioning, which may indirectly modulate semantic performance. Using a similar task design and procedure as in the SA task, the EXE task assesses executive/attention and decision-making abilities without the influence of semantics. As in the SA task, the task contains a verbal and a picture modality. For the verbal modality, the material includes 78 French words grouped into 26 trials. Each trial includes three words; two of them have the same initial and final letters (the target item and test item), while the third word is a distractor sharing only the initial or the final letter with the target item. The three words presented in each trial are semantically unrelated. The picture modality of the test uses drawn images instead of words. The pictures represent colored geometrical shapes. The material includes 78 pictures grouped into 26 trials. Each of the 26 trials includes three pictures, two of them representing the same geometrical shape or color (the target item and test item), while the third picture represents a distractor not sharing any of these features with the target item. The items of the verbal modality are matched for the number of letters with the word items of the SA task. Stimuli of version 1 and version 2 are matched for the number of letters. The three items are displayed on the computer screen for 8 s and subjects decide (using two response buttons) if the target item (on top of the screen) is related to the test item (on the bottom of the screen, either left or right) or the distractor item (on the bottom of the screen, either left or right, opposite to the test item). Thirteen test items appear at a left and 13 at a right bottom location. The lack of response during this 8-s time interval is recorded as an error. Figure 4 illustrates two trials of this test.

**Fig. 4 Fig4:**
[figure not shown]
Two illustrative trials of the executive function (EXE) task. **a** Trial in the verbal modality. For each trial participants have to decide which of the test items presented on the bottom of the screen begins *and* ends with the same letter as the target item (*abeille* (bee) - target item, *abysse* (abyss) - test item, *abri* (shelter) - distractor). **b** Trial in the picture modality. For each trial subjects have to decide which of the test items on the bottom of the screen has the same color *or* the same geometric form as the target item

#### Recognition of famous faces subtest

This test is adapted from the French BIP [59]. It is used to detect eventual negative effects of tDCS, decreasing the activity of the right ATL, which has been shown to play an important role in the recognition of known faces [7]. The material includes 28 pictures of faces of famous people. Each picture is displayed on the computer screen for 8 s. Participants have to decide if the face corresponds to one of the four professional categories (politician, actor, singer or TV presenter) by pressing one of four associated keys in the response box. The lack of response during this time interval is recorded as an error*.*

#### Ecological evaluation

Additionally, a semi-quantitative daily life communication questionnaire - *Echelle de Communication Verbale de Bordeaux* [60], which assesses the effectiveness of communication of patients with aphasia in everyday situations, is applied at baseline and at the 2-week post stimulation time point. This questionnaire was included in the protocol to count with an ecological measure of potential language improvements after tDCS and to assess its impact in patients’ day-to-day life.

### PET-MRI neuroimaging and EEG recording

Neuroimaging data (PET, MRI) are collected before the tDCS sessions (baseline) and 2 weeks after the tDCS sessions. These acquisitions provide all the sequences underlying the following explorations: cortical metabolism, gray matter thickness measures, white matter fiber tracking and functional connectivity. The examination is performed on a hybrid PET-MRI scanner (Signa 3 T GE Healthcare, USA). The injection of FDG (Fluoro-Deoxy-Glucose 2-18F: MÉTATRACE®, half-life of 109,77 min, or GLUSCAN®, half-life of 110 min) is performed if the blood glucose checked prior to injection is ≤ 1.5 g/l. Participants lie in neurosensory rest in a quiet and unlit room for at least 30 min post-injection, prior to image acquisition.

The acquisition of brain images with PET is conducted in *list mode*. It begins 30–40 min after injection of the radiopharmaceutical FDG tracer and lasts for 20 min (3 × 5 min). Images are reconstructed and corrected for physical phenomena. They are expressed in standard uptake value (SUV). Magnetic resonance images are acquired simultaneously and include two anatomical sequences (3D-T1, 3D-FLAIR), a functional imaging sequence (resting state fMRI) and a diffusion tensor imaging (DTI) sequence.

Additionally, prior to and following stimulation, the tDCS device (Startsim, NEuroelectrics, Barcelona) automatically records brain activity through EEG scalp electrodes (sampling at 1500 Hz, low-pass high-pass filter 4–40 Hz). Resting-state EEG recordings are obtained from 10 to 20 EEG system locations F4, F3, C4, C3, P4, P3 and T8, T7.

### Computational models of tDCS current magnitude and distribution

There is evidence that the thickness of the skull, the volume of the cerebrospinal fluid in the subdural space and the distance from the targeted region in the brain to the tDCS anode or cathode account for up to 50% of the spatial variation of the electric field strength [61–63]. Kim et al. [64] found that performance improvement in a working memory task correlated with the simulated current magnitude, suggesting that inconsistent behavioral outcomes of tDCS might be partly due to individual anatomical differences.

A computational approach of modeling should allow for defining if and how tDCS current magnitude and distribution in the heads of individuals can differ and how these differences will affect clinical outcomes. Individual computational models will be produced using the open-source tool ROAST [65] to simulate tDCS current magnitude and distribution using the anatomical 3D T1-weighted MRI images of each patient (Fig. 5). Then, correlation will be tested between model-estimated data for current magnitude values and clinical data, specifically the changes in scores in the SA task from baseline to post-stimulation. A region of interest (ROI) will be defined and the mean of the 5% highest electric field values in this region will be obtained for each patient. More specifically, we will define the left anterior/middle temporal lobe as our ROI, because this region is primarily damaged in SD and it is the region targeted during the stimulation. Finally, measures of thickness of the different tissue layers (skin, skull, cerebrospinal fluid volume, gray matter and white matter) and distances between the stimulation target (ATL) and the stimulating electrode will be obtained and regression models will be computed to identify specific features that most influence changes in current magnitudes. This will allow us to identify the characteristics that might influence patients’ responses to tDCS and help predict if an individual patient might benefit from tDCS treatment.

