## Introduction

Semantic dementia (SD), also referred to as the semantic variant of primary progressive aphasia (sv-PPA) [1], is part of the spectrum of frontotemporal lobar degeneration and constitutes one of the major clinical variants of this disorder [2]. The onset age of SD is frequently before 65 years [3] and it severely affects the ability to communicate, which generates a major impact on the family and socio-professional life of patients.

SD is characterized by a gradual and severe loss of conceptual knowledge, resulting in anomia, impaired word comprehension and speech that is fluent but empty of content [2], leaving grammar and speech articulation preserved [4]. Although the most prominent deficits concern word meaning [1, 4], SD might eventually cause deterioration of knowledge for all kinds of semantic concepts [5, 6] impacting on face recognition [7], object feature attribution [8], sound-picture matching [9] and object-use [10]. The damage to multi-modal semantic representations, besides the verbal domain, gave birth to the concept of semantic dementia [11]. It therefore appears that sv-PPA is a purely linguistic variant of SD [12] and/or that SD results from the evolving disease course of sv-PPA [13, 14].

At the anatomical level SD affects the anterior temporal lobe (ATL) of both hemispheres, predominantly in left lateralized regions [1, 4]. Correlation has been identified between gray matter loss in the ATL and different semantic tasks like picture naming [15, 16] and word-picture association [17]. It is associated with disruptions of functional connectivity between a broad range of brain regions across the temporal, frontal, parietal and occipital lobes, including visual and auditory association cortices [18]. Alterations of structural connectivity such as a white matter volume reduction in the left temporal lobe, the periventricular white matter and the corpus callosum [19], and damage to white matter tracts such as the inferior longitudinal fasciculus (ILF) and the uncinate fasciculus (UF) have also been found in SD [20]. Signs of cortical hypometabolism, which are a useful neuroimaging hallmark for diagnosis have mainly been found in the ATL cortices, sometimes extending to the subgenual region and the right anterior cingulate cortex [21].

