The purpose of this article is to present a clinical protocol (PHRC “STIM-SD”*)* implementing a multi-day tDCS regime in a large population of patients with SD (*n* = 60) specifically targeting the left ATL (with anodal stimulation) or the right ATL (with cathodal stimulation) to provide evidence for potential therapeutic effects and brain plasticity outlasting the duration of the treatment. This intervention builds on a previous pre-therapeutic double-blind, sham-controlled study by our team using a single tDCS session applied to the left and right ATL in patients with SD [45]. This approach allowed the comparison of left anodal (excitatory) to right cathodal (inhibitory) tDCS stimulation and showed that a single session of both left anodal and right cathodal tDCS resulted in transient but highly significant intra-semantic effects [45]. The goals of the present study include the evaluation of the potential therapeutic efficacy of periodical sessions of tDCS over the ATL during 10 days in language/semantic performance in patients with SD, the assessment of the time course of potential improvements, the exploration of potential effects on brain plasticity using functional connectivity measures (resting-state functional magnetic resonance imaging (fMRI)) and cortical metabolism (fluorodeoxyglucose positron emission tomography (FDG-PET)), the identification of the most efficient stimulation modality (left-anodal versus right-cathodal) and the identification of biomarkers such as ATL atrophy levels, which could be individually indicative of an efficient tDCS impact.

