In addition, baseline structural data (3D-T1 cortical thickness, DTI fiber tract analyses) and individualized models of tDCS current magnitude and distribution will be fundamental in understanding which anatomical features of our cohort most influence treatment efficacy, how the amount and spreading of electric current in the brain will impact individual clinical outcomes and possibly define a profile of patients that in the future would most benefit from tDCS.

Within neurodegenerative diseases specifically affecting language, SD is the most frequent variant of primary progressive aphasia [2], which contributes to the feasibility of the project in terms of patient recruitment. In the same vein, our National Reference Center for Rare or Early Onset Dementias provides a unique opportunity to recruit a large and homogeneous cohort of patients with SD. The active patient files on patients with early-stage SD in the three recruiting centers contained more than 20 patients with SD per year in 2013, 2014 and 2015. This shows that the total number of 60 patients with SD can be reached in the current project.

A potential tDCS treatment would be easily applicable, inexpensive and renewable when therapeutic effects disappear due to disease evolution. Significant effects of repetitive tDCS on language/semantics would also open an avenue for future tDCS trials targeting language non-related cortical regions such as areas subtending episodic memory, which is damaged, for example, in Alzheimer’s disease. More generally, the protocol might improve the understanding of neuroplasticity and its modulation through inhibitory and/or excitatory tDCS-driven cortical impact, while providing a rationale for appropriate stimulation modalities and for identifying brain regions likely to demonstrate relevant plasticity. Such insights could prove important for both tDCS and TMS trials, and their combination with behavioral language rehabilitation strategies, which might further enhance plasticity-related modulation.

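### The correlation of modelled current with SA change takes no account of disease stage or arm, so stage could be mistaken for a dose effect

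*Protocol article*

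**What the plan says.** The section on computational models of tDCS current plans an individual field model from each patient's T1 image. The value used is the average of the top 5% of field strengths in a left temporal region. The test itself is given as "correlation will be tested between model-estimated data for current magnitude values and clinical data, specifically the changes in scores in the SA task"; change here means the difference between the baseline and post-stimulation assessments. No covariate, arm term or restriction to stimulated patients is named.

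The same section plans a second step on tissue thickness, CSF and distance, but with current as the outcome: "regression models will be computed to identify specific features that most influence changes in current magnitudes". The Data analyses section studies baseline ATL cortical thickness separately, comparing responders with non-responders.

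Three other statements bear on the point:
- Among the determinants of field strength the article lists "the volume of the cerebrospinal fluid in the subdural space and the distance from the targeted region in the brain" to the electrode, together with skull thickness.
- The Introduction reports that "Correlation has been identified between gray matter loss in the ATL and different semantic tasks", and counts among the study goals the identification of "biomarkers such as ATL atrophy levels, which could be individually indicative of an efficient tDCS impact".
- The Discussion says that the models will help to understand "how the amount and spreading of electric current in the brain will impact individual clinical outcomes".

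**The concern.** Atrophy is a plausible common cause of both variables in the correlation. Loss of ATL tissue would be expected to enlarge the CSF space and change the distance from electrode to target, and so change the modelled field. Atrophy may also relate to SA change without any contribution from field strength, by two routes. The first is the protocol's own hypothesis that atrophy predicts response. The second is headroom on a task of 26 two-choice trials, which depends on how impaired the patient is at baseline. A two-variable correlation cannot separate these routes from an effect of current.

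Sham adds a second difficulty. Under Stimulation administration, sham patients get only the ramps, so a sustained field modelled for them is not a dose that they received. If they enter the correlation with that field, a true dose-response is diluted. If they enter with zero, the correlation becomes partly a comparison of arms.

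At stake is the causal reading, and the wish to use it to describe which patients would benefit. For pure prediction the confounding matters less.

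**Working it through.** **Plan's own figure.** None is stated for this correlation. The 80% power with 20 per group belongs to the primary comparison and does not bear on it.

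**Inputs from the article.** 20 patients per arm, hence 40 actively stimulated and 60 in all; significance level 5%. Skull thickness, CSF volume and distance together account for up to 50% of the spatial variation of the field. If that whole share were assigned to atrophy and read as variation between patients, r(atrophy, field) would be √0.50 = 0.71. This is a generous ceiling.

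**Inputs assumed.** r(atrophy, field) between 0.3 and 0.71, and r(atrophy, SA change) between 0.1 and 0.5. The article gives no coefficient for either.

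**Step 1: spurious correlation.** With no effect of current and atrophy as the only common cause,

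r(field, change) = r(atrophy, field) × r(atrophy, change).

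Examples: 0.5 × 0.3 = 0.15; 0.6 × 0.4 = 0.24; 0.7 × 0.5 = 0.35.

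**Step 2: chance of a nominally significant result.** By Fisher's z, the test statistic has mean atanh(r) × √(n − 3). For n = 40:
- r = 0.15: 0.151 × √37 = 0.92, two-sided rejection probability 15%.
- r = 0.24: 32%.
- r = 0.35: 0.365 × √37 = 2.22, rejection probability 60%.

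**Step 3: simulation over a wider range,** two-sided 5% test, no current effect:

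| r(atrophy, field) | r(atrophy, change) | n = 20 | n = 40 | n = 60 |
|---|---|---|---|---|
| 0.3 | 0.1 | 5% | 5% | 6% |
| 0.71 | 0.1 | 6% | 7% | 8% |
| 0.5 | 0.3 | 10% | 15% | 21% |
| 0.71 | 0.3 | 14% | 26% | 37% |
| 0.71 | 0.5 | 34% | 62% | 80% |

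**Step 4: effect of adjustment.** In the last row, the partial correlation given atrophy is significant in 5.1%, 4.8% and 4.9% of simulated trials, which is the nominal level. This supposes that the covariate captures atrophy fully. Cortical thickness does so only in part, so some bias would remain.

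**Step 5: price of the adjustment.** Collinearity multiplies the standard error of the field slope by about 1/√(1 − r²), where r is the correlation of field with thickness: 1.15 at r = 0.5 and 1.40 at r = 0.7. Residual variance explained by the covariates would offset part of this.

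**Step 6: should a slope different from sham be required?** Assume a true correlation of 0.4 under stimulation and 0 in sham; atanh(0.4) = 0.424. With 20 against 20 patients the standard error of the difference is √(1/17 + 1/17) = 0.343, and power is about 23%. With 40 against 20 it is √(1/37 + 1/17) = 0.293, and power is about 30%. A single correlation in 40 patients has about 73%. As a decision rule, the contrast with sham would usually miss a real relation.

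**The case against.** The strongest reply is that this faults brevity. The analysis serves a secondary, exploratory aim, and covariates and analysis sets for such work are often left to the full protocol or the analysis plan, neither of which is shown. The article does not ignore atrophy, and its claims about prediction are hedged. This stands in part: an unseen plan may already adjust. But the article does state the analysis. It gives a two-variable test, directs its anatomical regressions at current instead of SA change, and words part of the aim causally.

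A reader might infer more, namely that atrophy drives short-term decline, so that disease stage would be reported as a dose effect. The documents do not support that. The Introduction links atrophy to the level of semantic performance, not to change over the weeks between baseline and the 2-week assessment, and "biomarkers such as ATL atrophy levels, which could be individually indicative of an efficient tDCS impact" is put forward as a possibility. That tissue loss alters CSF volume and distance is a reasonable inference, but it is not stated. The 50% is an upper limit that includes skull thickness. Eligibility limits on aphasia severity, MMSE and FAB narrow the range of stage. The direction is open as well: more headroom favours gains in advanced patients, while progression favours losses.

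A reader might also infer that sham patients will be pooled with the field of the left-anodal arm. The article says only that each patient is modelled, and leaves open who enters the correlation.

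**Conclusion.** The point holds as a risk, not as a demonstrated bias. As described, the analysis cannot tell an effect of current from an effect of disease stage, although the article itself supplies the elements of a common cause and intends a partly causal reading. With 40 stimulated patients and no current effect, the false-positive rate lies anywhere between essentially nominal (5 to 7%, if atrophy correlates only 0.1 with SA change) and about 60% (0.7 with field, 0.5 with change), with 15% at 0.5 and 0.3. All of these rest on assumed correlations and on atrophy as the sole common cause. The sham point needs no such assumption: a sustained field modelled for a sham patient is not a delivered dose, and the text should say who enters the analysis. The primary comparison is not affected.

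**What to change.** Replace the correlation with a regression of the 2-week SA score on modelled field, adjusted for baseline SA score and baseline ATL cortical thickness. Fit it in actively stimulated patients, with arm in the model or separately by arm, because the two montages differ.

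Fit the same model in sham, with fields computed as if the patients had been stimulated, and report it as a descriptive negative control. Do not require a significant difference from sham, for which power would be low. Sham can reveal a stage effect that arises without stimulation, but not one in which atrophy modifies the response to stimulation; the thickness covariate is therefore needed in any case. Describe the result as exploratory.

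The change is to the analysis text only: SA scores, T1 images, cortical thickness and field models are already planned. The cost is a wider interval for the field slope, because field and thickness are likely to be correlated, and the interval will be wider still if the arms are analysed separately with 20 patients each.
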